## Abstract

**Background:**

Declines in cognitive functioning are a normal part of aging that can affect daily functioning and quality of life. This study will examine the impact of an exercise training program, and a combined exercise and cognitive training program, on the cognitive and physical functioning of older adults.

**Methods/Design:**

*Fit Bodies, Fine Minds *is a randomized, controlled trial. Community-dwelling adults, aged between 65 and 75 years, are randomly allocated to one of three groups for 16 weeks. The exercise-only group do three 60-minute exercise sessions per week. The exercise and cognitive training group do two 60-minute exercise sessions and one 60-minute cognitive training session per week. A no-training control group is contacted every 4 weeks. Measures of cognitive functioning, physical fitness and psychological well-being are taken at baseline (0 weeks), post-test (16 weeks) and 6-month follop (40 weeks). Qualitative responses to the program are taken at post-test.

**Discussion:**

With an increasingly aged population, interventions to improve the functioning and quality of life of older adults are particularly important. Exercise training, either alone or in combination with cognitive training, may be an effective means of optimizing cognitive functioning in older adults. This study will add to the growing evidence base on the effectiveness of these interventions.

**Trial Registration:**

Australian Clinical Trials Register: ACTRN012607000151437

## Background

Cognitive decline is a normal feature of aging. Memory difficulties, slowing mental speed, and decreased mental flexibility become evident in old age, even in older adults without dementia [1-5]. Normal, age-associated cognitive decline is related to declines in everyday functional abilities, and to increases in both formal and informal service use among older adults [6-8]. Interventions which improve cognitive functioning are therefore important for the well-being and quality of life of older adults.

### Exercise

Exercise has been suggested as an innovative approach to improving cognitive functioning in older adults. The benefits of exercise for general health and well-being in older adults are already well known [9].

Cross-sectional evidence suggests that older adults who are physically active display better cognitive functioning than their sedentary peers, in areas such as memory, reaction time, and visuospatial skills [10-13]. Prospective and longitudinal findings suggest that physical inactivity is predictive of subsequent cognitive decline and that changes in physical activity patterns over time are associated with changes in cognitive functioning [14-18].

Experimental studies of exercise training programs for older adults have generally shown improvements in cognitive functioning, particularly on measures of information processing speed and executive functioning (e.g. [19-21]). While some experimental studies have been less conclusive (e.g. [22-24]), this discrepancy is most likely attributable to methodological differences. These include differences in duration, intensity, and frequency of exercise training, along with differences in control groups, exclusion criteria, and cognitive outcome measures. A meta-analysis by Colcombe and Kramer [25] found that, overall, exercise interventions do have the potential to improve cognitive functioning in older adults, particularly mental speed and executive functioning. The meta-analysis also highlighted that the most beneficial programs are those which have exercise sessions of greater than 30 minutes duration, include aerobic *and *strength training components, and target adults aged between 65 and 70 years [25]. As this is a relatively new area of research, additional evidence is required to further support the claim that exercise training can improve cognition.

### Linking exercise and cognitive functioning

Several mechanisms have been suggested to explain the relationship between exercise and cognitive functioning. The main hypothesis is that exercise directly affects the structure and function of the brain. Increases in aerobic capacity (as a result of increases in exercise) are thought to increase cerebral blood flow, improve the transport and utilization of oxygen and glucose in the brain, promote neurogenesis (the creation of new nerve cells), and regulate neurotransmitter synthesis [14,15,17,18,26-28]. Some studies have found an association between improvements in aerobic capacity and improvements in cognitive function [19,21]. Other studies, however, have found no relationship [22-24,29]. More evidence is required to validate the idea of increased aerobic capacity as a prerequisite for improved cognitive functioning.

Psychological factors may play a role in mediating the relationship between exercise and cognition [30]. Exercise is known to improve psychological well-being [31], and psychological well-being has been associated with cognitive functioning [32,33]. A few studies of exercise training and cognitive training have included psychological measures (e.g. [22,34-38]), but results have been mixed. More research is required to elucidate the mediating role of psychological factors in the exercise-cognition relationship [30].

### Combination training

Some researchers have suggested that the benefits of exercise may be further enhanced by combining exercise training with cognitive training [36].

Cognitive training has been the traditional approach to improving cognitive functioning in older adults. It consists of learning and practicing skills and techniques to manage cognitively demanding situations (e.g. using mnemonics to aid recall). While these programs have been successful in improving the specific cognitive function targeted by the training (i.e. memory programs improve memory performance) [39-41], they do not have the potential to provide the physical *and *cognitive benefits offered by exercise training. A combination of exercise training and cognitive training, however, may provide the best of both worlds.

Fabre and colleagues [36] conducted an experimental study of combination training with four groups: aerobic training, cognitive training, aerobic *and *cognitive training, and control. They found that all three training groups improved significantly, with the combination training group (aerobic *and *cognitive training) improving significantly more than the other groups. These findings are limited, however, by the fact that the combination training group appear to have received a greater total number of training sessions per week than the other groups. Given that engaged lifestyles have been linked to cognitive performance in older adults [42-45], it is possible that the results of the combination training group could be a consequence of increased social interaction, rather than an added benefit of cognitive training. The potential of combined exercise and cognitive training could be better investigated by matching the overall training exposure of participants in a dual group to that of participants in an exercise training group.

### Feasibility

Little is known about older adults' perceptions of exercise training programs and combined exercise and cognitive training programs. While adherence and compliance data can provide some insight into the feasibility of a training program, qualitative feedback from participants provides information about satisfaction and acceptability. Collection of this type of information also provides an opportunity to identify specific strengths and weaknesses of a program, and to assess the real-life benefits of the training which cannot be measured with clinical tests or surveys [46,47].

### Aim

The aims of the present study are to:

(1) examine the impact of an exercise training program for older adults on cognitive and physical functioning,

(2) compare the impact of exercise training and a combined program of cognitive *and *exercise training for older adults (which has an equal number of total training sessions per week) on cognitive and physical functioning,

(3) examine associations between changes in aerobic capacity (as a result of exercise) and changes in cognitive functioning;

(4) examine associations between changes in psychological wellbeing (as a result of exercise) and changes in cognitive functioning; and

(5) identify older adults' perceptions of exercise training and combined exercise and cognitive training.

An exercise training program and a cognitive training program have been developed by the first author (SO), and will be evaluated in a randomized controlled trial. The content of these programs is based on previously successful training programs, and current theories regarding the relationships between exercise training, cognitive training, and cognitive functioning.

## Methods/Design

### Study design

*Fit Bodies, Fine Minds *is a 16-week, randomized controlled trial of exercise training and combined exercise *and *cognitive training for older adults. Participants are allocated to one of three groups: exercise-only training; exercise and cognitive training; no-training control. Assessments are conducted at baseline, post-test (16-weeks) and 6-month follow-up (40 weeks). The design is presented in Figure 1. The protocol was approved by the University of Queensland Medical Research Ethics Committee (Approval Number: HMS06/2303)

**Figure 1 F1:**
[figure not shown]
The design of the *Fit Bodies, Fine Minds *study.

### Setting

The program is conducted at *Riverside Fitness*, a privately-owned gym in Brisbane, Australia.

### Study population

The program is designed for community-dwelling older adults without cognitive impairment. Participants are recruited through healthy aging seminars at local churches, public radio broadcasts, and the *50+ Registry *(a registry of research volunteers aged over 50 years, coordinated by the Australasian Centre on Ageing at the University of Queensland). All interested people are provided with a Participant Information Sheet detailing the nature of the program.

Individuals are initially considered eligible if they are

(1) aged between 65 and 75 years,

(2) doing less than 60 minutes of moderate-intensity exercise per week,

(3) living within 10 km of *Riverside Fitness *and the University of Queensland; and

(4) available to participate in the program during business hours.

#### Screening

Individuals who meet the initial eligibility criteria take part in a telephone interview to screen for cognitive and health problems. People who score below 21 on the Telephone Interview of Cognitive Status (TICS) [48] are excluded from participating in the program. Individuals who report more than one serious health complaint (e.g. recent heart attack, uncontrolled diabetes, or uncontrolled hypertension) are required to obtain written permission from their general practitioner (GP) to take part in the program. Those unable to obtain GP permission are excluded from participating in the program. Individuals who report diagnoses of Alzheimer's Disease, dementia, or recent head injuries are also excluded from the program.

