##### Telephone Interview of Cognitive Status (TICS-m)

This is a brief telephone-administered dementia screening measure, modified slightly from the original to be more suitable for telephone use [48,53]. Participants complete a series of short cognitive tasks, such as counting backwards, remembering a list of 10 words, and answering general knowledge questions. Performance on the original TICS has been shown to be highly correlated with performance on the Mini-Mental State Examination [48,54]. The TICS-m is sensitive and specific [53]. A score of less than 30 (out of a possible 50) on the TICS-m is the cut-off for cognitive impairment [53].

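### The cognitive eligibility screen is inconsistent: the exclusion rule is below 21 on the TICS, but the instrument described is the TICS-m, with impairment below 30

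*Protocol article*

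**What the plan says.** Three places in the protocol article bear on this.

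- **Study population** sets the target: "The program is designed for community-dwelling older adults without cognitive impairment".
- **Screening, under Study population**, gives the only exclusion that depends on a cognitive test score: "People who score below 21 on the Telephone Interview of Cognitive Status (TICS) [48] are excluded from participating in the program". It adds exclusions based on self-report: "Individuals who report diagnoses of Alzheimer's Disease, dementia, or recent head injuries are also excluded from the program".
- **Telephone Interview of Cognitive Status (TICS-m), in the Screening part of Measurements**, describes the instrument. It has the same full name but is labelled TICS-m and presented as a slight modification of the original. The section ends with this cut-off: "A score of less than 30 (out of a possible 50) on the TICS-m is the cut-off for cognitive impairment". The same paragraph mentions the original TICS separately, when reporting its correlation with another cognitive examination.

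**The concern.** The exclusion rule and the instrument description differ in three respects: the version named, the threshold, and the reference cited for the threshold ([48] for 21, [53] for 30). The article offers no conversion between versions and no reason for an exclusion threshold lower than the impairment cut-off.

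The threshold defines the study population, and cognitive functioning is a primary outcome. The background and aims concern normal age-related decline. A reader of the results needs to know whether people whom the article classes as impaired could have entered, and at present cannot tell. The planned trial is small (99 participants, 33 per group), so even a few such entrants would be a noticeable part of the sample.

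**Working it through.** No sample-size, power or error-rate figure is involved. The check sets the statements side by side, counts the scores between the two cut-offs, and asks whether any reading makes all the statements correct.

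**Inputs**

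| Item | Screening (under Study population) | TICS-m section (under Measurements) |
|---|---|---|
| Version named | TICS | TICS-m |
| Threshold | below 21 | below 30 |
| Scale maximum | not given | 50 |
| Reference for the threshold | [48] | [53] |
| Role of the threshold | exclusion rule | cut-off for impairment |

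**Step 1. Scores between the cut-offs, if both apply to the TICS-m.** Scores from 21 upward pass the exclusion rule. Scores of 29 and lower count as impaired. The overlap is 21 to 29 inclusive: 29 − 21 + 1 = 9 whole-number scores, equal to 30 − 21 = 9 points.

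**Step 2. The possible readings.**

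1. *The TICS-m is given and the rule of 21 is applied.* The nine scores in Step 1 are admitted although the TICS-m section classes them as impaired. This contradicts the target in Study population.
2. *The original TICS is given and the rule of 21 is applied.* The numbers 21 and 30 then belong to different versions, so the subtraction in Step 1 has no meaning. Nobody is shown to be misclassified. But the Measurements section describes a version and a cut-off that have no function in eligibility, and the instrument in use is not the one described.
3. *The TICS-m is given and the cut-off of 30 is applied.* The exclusion rule in Screening then names the wrong version and the wrong number.

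Each reading leaves at least one section wrong. Readings 1 and 3 fit the Measurements section better, because the TICS-m is the only cognitive screen described there. Reading 2 fits the wording and citation of the exclusion rule better. The article does not settle which holds.

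**Step 3. Does another criterion close the gap?** The remaining cognitive exclusions are reported diagnoses of Alzheimer's disease or dementia, and recent head injuries. They narrow the problem but do not catch an undiagnosed low scorer, whom a telephone test is there to find.

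**Step 4. How many people are affected?** The article gives no distribution of screening scores and no range for the original TICS. The share of volunteers scoring 21 to 29 cannot be computed.

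**The case against.** The best defence is that the exclusion rule is complete in itself. It names the TICS and cites the source that the article elsewhere attaches to the original version, so it can be read as the original instrument with its own threshold. The article would then contain a mismatched instrument description and no error in who is enrolled. That reading is possible and cannot be ruled out, so four stronger inferences a reader might draw are not supported:

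- **That the trial enrols impaired people.** This follows only if the TICS-m is given together with the rule of 21. Likewise, the nine-score band exists only on that reading.
- **That there are two competing exclusion rules**, so that two screeners would decide differently on the same person. Only the Screening section excludes anyone on a score. The TICS-m section reports a cut-off for impairment, and the conflict arises when it is read together with the stated target population. What is truly ambiguous is which version is given.
- **That the comparison between groups is biased.** According to Randomization, people are allocated only after meeting the screening requirements, so any low scorers are distributed over all three arms by chance. Extra variability or a different response among them is conceivable, but the article gives nothing from which to quantify it.
- **That 30 is the intended threshold.** The article does not show which number was meant.

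These limits stand, and they reduce the consequence. They do not remove the inconsistency, because the defence itself requires the TICS-m section to be wrong about the instrument in use. Nor is this a detail left out of a condensed article: both versions and both numbers are stated.

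**Conclusion.** The point holds as an inconsistency in the definition of the study population. The article gives one version and threshold for exclusion and another for the instrument and its impairment cut-off, and the two cannot both be right alongside the stated target.

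The size depends on an assumption the article does not resolve. If the TICS-m is given with the rule of 21, nine scores (21 to 29 of 50) are admitted although classed as impaired. If the original TICS is given, no band can be stated and the fault lies in the instrument description. In either case the effect is on who is enrolled and to whom the results apply, and the proportion affected is unknown. The text should be corrected because eligibility depends on it and the correction is nearly free.

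**What to change.** Reconcile Study population, Screening and the TICS-m section. Name the one version actually administered, and state that version's own cut-off as the exclusion rule in both the Screening section and the Measurements section, consistent with a target population free of cognitive impairment. The trial team has to supply which version and threshold apply, since the article does not show it and none is proposed here.

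If the TICS-m was used with the rule of 21, check the screening logs for scores of 21 to 29 and report how many of those people were enrolled. On any other reading this check does not apply.

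The cost is a short text correction and, where needed, a review of the logs. If the correction raises the threshold in use, a few more people may fail screening.

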#### Informed consent

Participants provide signed informed consent prior to baseline testing.

### Sample size

Ninety-nine participants will be recruited for the study. A sample size of 12 participants in each of the three groups would enable detection of a within-group difference, from baseline to post-test, of 1 item (SD = 1.1) on Digit Span and 184 milliseconds (SD = 198) on Choice Reaction Time. Twenty participants in each group would enable detection of a between-group difference, at post-test, of 2 items (SD = 2.2) on Digit Span. Twenty-nine participants in each group would enable detection of a between-group difference, at post-test, of 118.8 milliseconds (SD = 160) on Choice Reaction Time. These sample size calculations assume a two-tailed alpha level of 0.05 and a power of 80%. The effect sizes and standard deviations are based on results from previous studies of physical activity for cognitive functioning in older adults (e.g. [11,49]). To account for attrition over time, the required sample size (29) is increased by 10% to 33 participants per group.

### Randomization

Participants are randomly allocated using block randomization [50]. Each block contains one exercise-only group allocation, one combined exercise *and *cognitive training group allocation, and one control group allocation. The order of the groups within each block is randomly generated by selecting papers from a box. The box contains three papers marked *Exercise Only*, *Exercise & Cognition*, and *Control*, respectively. This process is repeated to generate a list of 25 blocks. Each time a participant meets the eligibility criteria and screening requirements, they are allocated to the next available place on the list.

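### The randomization list holds 75 places (25 blocks of three), but the plan is to recruit 99, so 24 participants have no place on it

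*Protocol article*

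**What the plan says.** Two sections of the protocol article bear on this.

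**Sample size.** "Ninety-nine participants will be recruited for the study". The largest of the listed requirements is 29 per group, for a "between-group difference, at post-test, of 118.8 milliseconds (SD = 160) on Choice Reaction Time", at two-sided 0.05 and 80% power. The attrition allowance follows: "the required sample size (29) is increased by 10% to 33 participants per group". The same section also gives 20 per group for a "between-group difference, at post-test, of 2 items (SD = 2.2) on Digit Span" and 12 per group for the within-group changes on both tests.

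**Randomization.** "Each block contains one exercise-only group allocation", together with one for the combined group and one for control. The physical procedure confirms the block size: "The box contains three papers marked" with the three group names. Then: "This process is repeated to generate a list of 25 blocks". Each person who passes eligibility and screening takes the next unused slot. Neither section mentions a second list, an extension of the list, or any other block size.

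**The concern.** The number of people to be randomized and the list that allocates them should agree, and here they differ by 24. There are two ways to proceed, and neither is covered by the text:

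- If the list governs, randomization ends at 25 per group. That is below the 29 per group required for Choice Reaction Time even before any attrition.
- If the target governs, participants 76 to 99 are allocated by a sequence that the article does not describe.

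As written, a reader cannot tell whether the trial randomizes 75 or 99 people, or whether the power stated for the comparison that fixed the sample size applies.

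**Working it through.** **Inputs.** From Sample size: difference δ = 118.8 ms and SD σ = 160 ms (Choice Reaction Time, between groups); 2 items, SD 2.2 (Digit Span, between groups); 1 item, SD 1.1, and 184 ms, SD 198 (within group); two-sided α = 0.05; power 80%; attrition 10%; 33 per group; 99 in total. From Randomization: 3 places per block, 25 blocks.

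**Step 1: reproduce the plan's sample size.** With the normal approximation,

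n = 2 × [σ(z₀.₉₇₅ + z₀.₈₀)/δ]² = 2 × [160 × (1.960 + 0.842)/118.8]² = 28.5, rounded up to 29 per group.

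The t-based solution is 29.5, and power at exactly 29 is 79.3%, which is close to the stated figure. For attrition, 29/(1 − 0.10) = 32.2, rounded up to 33, and 33 × 3 = 99. The other stated sizes also reproduce with t-tests: 20.0 per group for between-group Digit Span (20 stated), and 11.6 and 11.2 for the within-group changes (12 stated). The Sample size section is internally sound.

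**Step 2: capacity of the list.**

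- 25 blocks × 3 places = 75 places, 25 per group.
- Blocks needed for 99: 99/3 = 33.
- Shortfall: 33 − 25 = 8 blocks; 99 − 75 = 24 places; 24/99 = 24% of the target.

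**Step 3: power if recruitment stopped at 75.** The standardized differences are 118.8/160 = 0.7425 (Choice Reaction Time) and 2/2.2 = 0.909 (Digit Span). Normal approximation: power = Φ(d/√(2/n) − 1.96). At n = 25 for Choice Reaction Time this is Φ(0.7425/0.2828 − 1.96) = Φ(0.665) = 75%. The two-sample t-test gives slightly less. After 10% attrition, 25 × 0.9 = 22.5 per group, or 22 in whole people.

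| Per group | Choice Reaction Time, t (normal) | Digit Span between groups, t (normal) |
|---|---|---|
| 33 (planned) | 84.4% (85.5%) | 95.3% (95.8%) |
| 29.7 (planned, less 10%) | 80.3% (81.6%) | 93.1% (93.9%) |
| 25 (list) | 73.0% (74.7%) | 88.3% (89.5%) |
| 22.5 (list, less 10%) | 68.2% (70.2%) | 84.6% (86.2%) |
| 22 (rounded down) | 67.2% (69.2%) | 83.8% (85.4%) |

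The within-group targets keep 98% power or more at both 25 and 22 per group. Put another way, the Choice Reaction Time difference detectable with 80% power (t-test) would rise from the planned 118.8 ms to 129.4 ms at 25 per group and 136.7 ms at 22.5.

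**The case against.** **The target may simply be right and the block count a slip.** The Sample size section states 99 plainly and its arithmetic holds, so a wrong block count with the target intact is at least as plausible as the reverse. In that case no power is lost. This stands: the power loss is conditional on recruitment stopping at 75. It does not remove the contradiction, because the article does not show which figure is wrong.

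**A journal article condenses a fuller protocol.** That excuses omissions. It does not excuse two figures, both stated outright, that cannot both be true. Nor can 75 be read as the number left after attrition: slots are used when a person passes screening, before any loss, and 25 per group is below even the uninflated 29.

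**A reader might infer that the last 24 allocations must be improvised by unblinded staff, opening selection bias.** The documents do not support this. The paper-drawing procedure is repeatable, and eight more draws would extend the list in the same way. The Blinding section says that researchers are not blind to allocation, but nothing says who draws the blocks or who would extend the list. With fixed blocks of three and unblinded researchers, blocks drawn later by the same method would be no more predictable than the first 25. Any worry about predictability concerns the whole list and is a separate matter. What remains is that no rule is stated for participants 76 to 99.

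**A reader might also infer that the whole trial would fall short of its stated power at 75.** It would not. Only the between-group Choice Reaction Time target drops below 80%.

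**Conclusion.** The plan is wrong as written. The list has 75 places and the recruitment target is 99, a gap of 8 blocks or 24 participants, with no stated rule to bridge it. That part is plain arithmetic and rests on no assumption.

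The effect on power is conditional and limited to one comparison. If the list governs, between-group Choice Reaction Time has about 73% power with complete follow-up and about 67–68% after 10% attrition, against 80% stated. These figures take the plan's own difference, SD, alpha and attrition rate, and a two-sample t-test at post-test without covariates. The between-group Digit Span and within-group targets still exceed 80%. If 99 are recruited, no power is lost and the remaining fault is an incomplete allocation list. The documents do not support a claim of actual selection bias or of a general loss of power.

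The point needs correcting because the number randomized and the allocation sequence are basic to the trial, and the two sections cannot both be followed.

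**What to change.** Reconcile the Randomization and Sample size sections in one of two ways.

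1. **If 99 is the target:** change 25 to at least 33 blocks (33 × 3 = 99 places), all generated in advance by the drawing method the Randomization section already describes. With 33 per group, Choice Reaction Time power is about 84%, and about 80% after 10% attrition, as planned.
2. **If 75 is the true target:** restate the sample size as 75 (25 per group) and the between-group Choice Reaction Time power as about 67–73%, depending on attrition. Attach that figure to this comparison only; the Digit Span and within-group statements still hold at 80% or better.

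The first option costs one corrected figure and eight more draws from the box. The second costs a rewritten Sample size paragraph. Neither places any burden on participants.

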### Blinding

For logistical reasons, participants, researchers, and instructors are not blind to the allocation of participants.

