#### Modes of assessment

Screening is conducted by telephone. Cognitive and physical assessments are conducted face-to-face at the University of Queensland. Cognitive assessments are conducted by SO. Each cognitive assessment session lasts for 90 minutes. Physical assessments are conducted by an exercise physiologist and last for 30 minutes. Physical assessments are conducted immediately after the cognitive assessments. Self-administered questionnaires are used to assess psychological wellbeing. These are provided after the cognitive assessment, with participants instructed to complete them at home and mail them back within seven days using a provided reply-paid envelope. Participant perceptions of the two training programs are collected using a feedback form included with the other self-report instruments. Only training participants complete this feedback form.

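### Allocation is triggered by passing telephone screening, apparently before baseline testing, and fixed blocks of three in an unblinded trial make every third place predictable

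*Protocol article*

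**What the plan says.** All references are to the protocol article.

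- **Trigger for allocation (Randomization):** "Each time a participant meets the eligibility criteria and screening requirements, they are allocated to the next available place on the list".
- **Sequence (Randomization):** "Each block contains one exercise-only group allocation", with one combined-training and one control place besides. "The box contains three papers marked" with the three group names, and the order of drawing sets the order within a block. "This process is repeated to generate a list of 25 blocks".
- **Screening (Screening; Modes of assessment):** "Screening is conducted by telephone". It covers a cognitive screen and health questions. Assessment stages lists it separately from the baseline, 16-week and 40-week assessments.
- **Consent (Informed consent):** "Participants provide signed informed consent prior to baseline testing". Its position relative to allocation is not given.
- **Blinding:** "participants, researchers, and instructors are not blind to the allocation of participants".
- **Assessor (Aim; Modes of assessment):** "An exercise training program and a cognitive training program have been developed by the first author", and the same person conducts the cognitive assessments.

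The text does not say who enrols, who holds the list or whether it is hidden.

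**The concern.** Read together, these sections put allocation between the telephone interview and the first outcome measurement, in a trial with no blinding. Three things follow.

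1. **Baseline assessment.** The program developer can know a participant's group while giving the baseline tests of the primary cognitive outcomes. The Analyses section assesses change over time and applies a Reliable Change Index relative to each person's own baseline, so a shift at baseline passes straight into those results.
2. **Loss between allocation and baseline.** Controls receive no formal intervention, and participants know their group. Someone disappointed with the control group can leave before baseline. If this happens more in one arm, the groups that reach baseline are no longer those that randomization formed. The 10% attrition allowance in Sample size protects the numbers, not the comparison.
3. **Predictability at entry.** Some entry steps leave room for judgement, such as self-reported weekly exercise and what counts as a serious health complaint needing the general practitioner's permission. A recruiter who can predict the next place could, even unintentionally, let that affect who enters and when.

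**Working it through.** **Order of events.** Randomization names one condition for receiving a place: eligibility and screening met. Screening is by telephone. Baseline testing is at the university, with a 90-minute cognitive session followed by a 30-minute physical one. Assessment stages treats the two as distinct. The natural reading is screening, then allocation, then baseline. Consent must precede baseline, but the text allows it either before or after allocation.

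**Predictability.** The plan gives no figure of its own to reproduce here.

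*Inputs:* block size 3, one place per arm, 25 blocks (Randomization). *Assumption:* the guesser knows the block size and all past allocations and always names the group with most places left in the block. The list itself stays hidden.

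The chance of a correct guess at each place is (most places left for any one arm) / (places left in the block):

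- first place: 1/3
- second place: 1/2
- third place: 1/1

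Average = (1/3 + 1/2 + 1)/3 = (11/6)/3 = 11/18 = 61.1%, against 1/3 = 33.3% by chance. One place in three is certain.

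The list has 25 × 3 = 75 places. (The plan is to recruit 99, so the list is 24 places short; that is a separate matter.) Over 75 places, 25 are known with certainty, and the expected number of correct guesses is 75 × 11/18 = 45.8, against 25 by chance.

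**Would larger blocks cure this?** The same rule for a block of 6, averaged over possible histories, gives 1/3, 2/5, 1/2, 8/15, 3/5 and 1. Their sum is 3.367, and 3.367/6 = 56.1%. Exact enumeration gives the following:

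| Block size | Places known with certainty | Correct guesses |
|---|---|---|
| 3 | 33.3% | 61.1% |
| 6 | 20.0% | 56.1% |
| 9 | 14.3% | 53.2% |

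Larger blocks of known size help only modestly. Mixing sizes without disclosing them should lower predictability further; that gain was not calculated.

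**How a baseline shift enters the result.** If knowledge of the group moves a baseline score by δ, the observed change is post − (baseline + δ) = true change − δ. Lower scores recorded at baseline in a training arm would therefore look like improvement on tests where higher is better. The documents give no basis for a value of δ, so none is assumed.

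**Which measures are exposed.** Most exposed are tests that the examiner gives, times or scores: story and word-list recall, digit span, Stroop times and errors, sorting-rule descriptions, and timed daily tasks with error adjustment. The two reaction-time tasks are recorded by computer in milliseconds. The walk test is distance in metres. The psychological questionnaires are completed at home and mailed. For these, knowledge of the group could act through encouragement or effort, or through the participant's own answers, but not through examiner scoring of responses.

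**The case against.** The strongest case on the other side is that a reader might infer more than the text states.

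- **Allocation before consent.** This is not established. Consent is fixed only relative to baseline testing, so it may come first. What stands is that the allocation rule does not require it.
- **An open list, operated by unblinded staff.** This is not established either. Randomization uses the passive voice and names no allocator. Saying that researchers are not blind concerns knowledge of assigned groups, not who sees the next place. A condensed article may leave concealment to the full protocol, so its silence is not itself a defect. The predictability result does not need an open list; it needs only knowledge of the block size and past allocations.
- **People lost before baseline leave no data.** This is wrong. Screening collects demographics, health information and a telephone cognitive score, so early losses could be counted and compared by arm. They would lack baseline outcomes.
- **Every change score is contaminated.** This is overstated, given the computer-timed tasks, the walk distance and the mailed questionnaires.

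It is also fair to say that 61.1% measures predictability, not bias in an outcome, and that Figure 1, which was not available, might show a different order. These limits narrow the point. They do not remove the stated trigger, the fixed block size or the absence of blinding.

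**Conclusion.** The point holds in this form. As written, allocation follows telephone screening and apparently precedes baseline testing, in a trial where participants and researchers know the groups and the program developer gives the cognitive tests. Examiner-administered baseline scores are open to influence by knowledge of the group, and participants assigned to control can be lost before any baseline outcome is measured. Fixed blocks of three make one place in three certain and 61.1% of places guessable, against 33.3% by chance, for someone who knows the block size and past allocations.

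This rests on reading the Randomization rule literally and on Figure 1 not contradicting it. The effect on any outcome cannot be sized from the documents. The logistical reasons given for the lack of blinding may explain unblinded post-tests. They do not explain unblinded baselines, which a change in the order of events would avoid. The flaw is worth correcting before further enrolment, because a distorted baseline or a missing one cannot be recovered in the analysis.

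**What to change.** Reword the Randomization section to say that:

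1. allocation takes place only after signed consent and completed baseline assessment;
2. the next place comes from sequentially numbered, opaque, sealed envelopes, or from a list kept from those who recruit and assess;
3. as a secondary measure, block sizes vary at random (for example 3, 6 and 9) and are not disclosed to recruiters.

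The questionnaires go home after the cognitive session and have seven days to come back. The text should therefore say whether their return counts as part of completed baseline assessment; if it does not, they may be answered with the group known.

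If anyone has already been allocated under the present rule, report by arm how many were lost between allocation and baseline, and compare them on the screening data.

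The cost is a few sentences and a set of envelopes. Participants learn their group slightly later, and final group sizes may differ by a few. No extra assessor is needed for the baseline to become blind to group. The change does nothing for the unblinded post-test and follow-up assessments.
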